### Subgroup Analyses

We will repeat the primary outcome analysis for those with and without the following baseline characteristics: Male sex, resistant hypertension (defined as ≥ 3 antihypertensive medications), CHF, CKD, diabetes and (separately) use of the major BP medication classes (ACEI, ARB, CCB, diuretic, beta-blocker).

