## **C) BEDMED-Frail TRIAL PROTOCOL:**

**Design:** Event-driven Prospective Randomized Open Blinded End-Point (PROBE) Randomized Trial.

**Population:** Hypertensive long-term care (LTC) residents using BP lowering medication.

**Inclusion Criteria:** 1) Hypertension diagnosis as indicated by  $\geq 2$  such billing diagnoses at any time in the administrative claims data by any provider; 2)  $\geq 1$  ONCE DAILY BP lowering medication; 3) LTC resident in a participating facility.

**Exclusion Criteria:** 1) Personal history of glaucoma or use of glaucoma medications. *Glaucoma is an exclusion because nocturnal hypotension (i.e. excessively low blood pressure while sleeping) has been associated with ischemic optic neuropathy in such patients.* 2) Any family member or treating physician (all of whom will be notified of the LTC facilities participation in this initiative) requesting the patient not participate.

**Intervention:** Switching (*one at a time as tolerated*) one or more morning BP meds to BEDTIME (or *maintaining* bedtime BP meds if already taken at that time). The timing of loop diuretics (which can cause meaningful diuresis), and BP medications taken more than once a day, will not be altered. If more than one medication change is needed, each change will take place one week apart.

**Comparator:** Maintaining (or switching to) morning BP medication use.

**Outcomes:** Outcomes are drawn from administrative claims data and quarterly MDS reporting. The Alberta SPOR Data Platform will monitor our primary outcomes quarterly during the trial, and the trial will conclude once 301 participants have experienced primary outcome events. Outcomes include:

- Primary: Composite of all-cause death and hospital admission or emergency room visit for acute coronary syndrome/MI, heart failure, or stroke (using administrative data based case definitions with validated coding algorithms).
- Secondary: 1) Each element of the primary outcome alone; 2) All-cause hospitalization; 3) Acute Care Costs (from each admissions resource intensity weight & length of stay).

*The following additional outcomes (unless otherwise indicated) will be determined from the first available **MDS Quarterly assessment** in the 3 - 6 month window post randomization:*

- Safety: 1) Fell (past 30 days); 2) Any Fracture (from administrative claims data over the study duration – not MDS data); 3) Full Thickness Skin Ulceration (stage 3 or 4).

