Overall: We expect to randomize a minimum of 1200 residents and observe over a roughly 2-3 year period until 301 primary outcomes have occurred (with those outcomes being reported to us quarterly by the Alberta SPOR Data Platform). At a minimum this will provide sufficient power (80% power to detect a 27.6% difference) to validate or refute the MAPEC trials claim of a 55% reduction in mortality, and will likely provide substantial additional fidelity to detect smaller differences that are not currently calculable (as a result of meaningful covariates, continuous outcomes, and the expectation of additional facilities joining the project in coming months).

**E) Confirmation of data accuracy:** Prior to randomization the data steward will produce a list of all residents they believe to currently reside at each of the participating facilities. They will simultaneously request a list of all admitted residents from each participating facility and will compare these two lists to ensure there are no errors in identifying residents.

**F) Recruitment / Patient Flow:** (Flow Diagram - appendix pg. 6)

1. Informing Patients / Families / Primary Care Providers: Prior to facilities being randomized, we will send letters to all next of kin, and all attending primary care providers, notifying them that this study is taking place and that blood pressure medications might have their timing switched to bedtime. If family or physicians object, we will ask them to e-mail or call a toll free number to let us know the resident's name and the facility they reside in and we will exclude them from the timing change. A number will also be provided to speak with a BedMed physician if families or physicians have questions about the study.
2. Randomization: A minimum of one month after the last notification letter is mailed, eligible residents who have not opted out of participation will be randomized using random blocks of 2 or 4 with no stratification.

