| 08-10-2024 | 11-10-2024 | 
1. Sub-study: During the course of data analysis, the primary outcome of 'major adverse cardiovascular events' trended to benefit (although not statistically significant) and 'unplanned all-cause hospitalization/emergency department (ED) visit' saw a statistically significant reduction of 28% (<math>p = 0.01</math>). To further explore this finding, long term care facility residents will be observed for an additional 1 year post planned final analysis with a repeat analysis of all outcomes conducted in March of 2025. Several months after the end of data collection we reached out to all participating facilities and were told that none of the participants' antihypertensive medication timings had been changed. We would like to ask them to continue with those allocations, given we have demonstrated no harm and the possibility of benefit for bedtime prescribing which requires further exploration.
 
2. Chronotype category analysis: Given a recent antihypertensive timing trial (TIME) demonstrated that chronotype, which is defined by the time of day people are most active (often referred to as early birds or night owls), might influence the effect of antihypertensive timing on cardiovascular events, we would like to explore this with the BedMed-Frail data as well. Although chronotype itself is not available in the RAI-MDS data, there are three things which we feel may create a rough approximation for chronotype. These are the description of the time of day when patients are active (morning, midday, evening), problems with insomnia, and use of sleeping pills. We would define early birds as being those who are active in the morning and not the evening and we would define night owls as being those who are active in the evening but not the morning or those who have insomnia or are using sleeping pills. We would like to repeat the analysis of the primary outcome and the analysis of all cause unplanned hospitalization/ED visits using early bird and night owl as covariates in the survival analysis carried out for each of these outcomes, as well as including an interaction term between allocation and each of these chronotype covariates. In so doing, we would be looking to see if the hazard ratio and p-value for those covariates suggests an influence of chronotype on the effects of medication timing on mortality and morbidity.
 |

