### Selecting regression covariates

Analyses of dichotomous outcomes will use a maximum of 1 covariate per 10 outcomes, and analyses of continuous outcomes will use a maximum of 1 covariate per 20 randomized subjects. The covariate list for each analysis is predefined in table 2, and all are measured at baseline. We will always use the maximum number of covariates possible, selected in the order given (i.e. we will not undertake stepwise addition or subtraction). As we go down the covariate list, if one covariate has too many levels to be accommodated by the remaining number of outcomes or participants (e.g. facility, or level of care) we will skip it and go to the next covariate in the list.

| Table 2 Analysis Plan        |                          |                                                                                                  |
|-------------------------------------|--------------------------|--------------------------------------------------------------------------------------------------|
| Outcome                      | Method            | Baseline Covariates                                                                       |
| Primary                      |                          |                                                                                                  |
| Major adverse cardiovascular events | Cox Proportional Hazards | Age <70, Gender, Facility/Level of Care specific mortality rate (prior 3 years), New admission*, |

|                                                                                     |                          |                                                                                                                                                                                                                                                                                                                                |
|-------------------------------------------------------------------------------------|--------------------------|--------------------------------------------------------------------------------------------------------------------------------------------------------------------------------------------------------------------------------------------------------------------------------------------------------------------------------|

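### The ten SAP subgroup factors are analysed by separate refits with no interaction test, so the plan never tests whether the effect differs and chance differences between strata can be read as effect modification

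*Combined protocol and SAP*

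**What the plan says.** The SAP section *Subgroup Analyses* reads: "We will repeat the primary outcome analysis for those with and without the following baseline characteristics". The factors come in two groups:

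- Five patient characteristics: "Male sex, resistant hypertension (defined as ≥ 3 antihypertensive medications), CHF, CKD, diabetes".
- Five drug classes, taken separately: "use of the major BP medication classes (ACEI, ARB, CCB, diuretic, beta-blocker".

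That makes ten factors and 20 stratum-specific fits. The analysis being repeated is the Table 2 primary model, "Cox Proportional Hazards" with a predefined, ordered covariate list. The length of that list is governed by the rule in *Selecting regression covariates*: "Analyses of dichotomous outcomes will use a maximum of 1 covariate per 10 outcomes".

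For these ten factors the SAP names no interaction test, no multiplicity approach, no expected direction and no rule for interpreting differences. The protocol's own statistical analysis paragraph plans no subgroup analysis. The only interaction term in the documents is in the amendment log entry submitted in October 2024, which describes a chronotype analysis "as well as including an interaction term between allocation and each of these chronotype covariates". It does not extend to the ten SAP factors.

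**The concern.** The reason to look at a factor with and without is to see whether the treatment effect depends on it. Two separate fits each test whether there is an effect in that stratum. Neither tests whether the two effects differ. A result that is significant in one stratum and not in the other is weak evidence of a difference, because each stratum has fewer events and so less power than the whole trial.

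At stake is what is concluded about sex, heart failure, kidney disease, diabetes or drug class. A uniform benefit could look like a pattern of responders and non-responders and so steer who is thought to gain from bedtime dosing. The primary result is not affected.

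**Working it through.** **Inputs.** Events: 301 (protocol, section C: "the trial will conclude once 301 participants have experienced primary outcome events"). Power and effect: "80% power to detect a 27.6% difference" (section D), read as HR 1 − 0.276 = 0.724. Alpha is 0.05 (section D); its sidedness is not stated and two-sided is assumed. Allocation is 1:1 (amendment log, November 2019 entry). The share of events in each stratum is not given, so 50/50, 30/70 and 20/80 are assumed.

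**1. Reproduce the plan's figure.** Schoenfeld events = 4(1.960 + 0.842)² / (ln 0.724)² = 4 × 7.849 / 0.1043 = 301, an exact match. A one-sided alpha gives 238, which supports the two-sided reading.

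**2. One factor, true HR 0.724 in both strata.** Power in a stratum with e events is Φ(0.3230 × √e / 2 − 1.96). The chance that exactly one stratum is significant is p₁(1 − p₂) + p₂(1 − p₁).

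| Event split | Events | Power in each stratum | Exactly one significant |
|---|---|---|---|
| 50/50 | 150.5 / 150.5 | 51% / 51% | 50% |
| 30/70 | 90 / 211 | 34% / 65% | 55% |
| 20/80 | 60 / 241 | 24% / 71% | 61% |

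**3. Ten factors together.** In a simulation, each of the 301 events falls in the bedtime arm with probability HR/(1 + HR), and ten independent binary factors are assigned with no effect modification.

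- True HR 0.724: about 91–95% of trials have at least one discordant pair, and on average about 5 of the 10 pairs are discordant.
- True HR 1.0: about 41% of trials have at least one significant stratum.
- Ten interaction tests at 0.05: 1 − 0.95¹⁰ = 40% have at least one false positive if independent (37–40% simulated), whichever HR is true.

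**4. What an interaction test can detect.** The standard error of the log ratio of HRs is √(4/e₁ + 4/e₂).

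| Event split | SE | Power for a ratio of 0.724 | Ratio detectable with 80% power |
|---|---|---|---|
| 50/50 | 0.231 | 29% | 0.52 |
| 30/70 | 0.252 | 25% | 0.49 |
| 20/80 | 0.288 | 20% | 0.45 |

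**5. Covariate rule, if reapplied within strata.** The Table 2 primary list has 18 entries, with eight ahead of Facility and nine after it. At 30/70, 90 events allow 9 covariates. The first eight enter and one slot remains. Facility is skipped (unless it needs only one term), one medication count enters, and the last eight entries are lost. In the other stratum, 211 events allow 21, leaving 13 after the first eight. Facility enters if it needs 13 terms or fewer; if not, all nine later covariates enter. Either way the two strata carry different models. At an even split both have 15 slots and the mismatch disappears.

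**The case against.** - **Prediction of misreading.** A reader might infer that chance differences will be taken as effect modification. The documents do not support that: the SAP sentence mentions no p-values and no rule for claiming a difference, so only *can be* is defensible. Separate fits also yield an HR and interval per stratum, from which anyone can approximate an interaction test. This stands in part. The information survives, but nothing commits the team to the test, and the approximation is cleanest when both strata use the same covariates.

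- **The no-effect case.** It is tempting to set 1 − 0.95²⁰ = 64% for 20 stratum tests against 5% for an interaction test. That comparison is unfair. The ten pairs re-divide the same residents, so the 20 tests cannot be independent, and a family-wise rate is being set against a per-test rate. Like for like, the figures are about 41% and 40%. This objection stands in full.

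- **The covariate mismatch.** A reader might infer that paired strata will certainly be adjusted differently. That requires the cap to be reapplied within strata, which the SAP does not say, and an uneven split of events. What happens to Facility depends on the number of facilities, which is not given. Allocation is randomised, so differing adjustment would not confound either HR. This point is therefore conditional and secondary.

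- **Low interaction power.** An interaction test would miss most moderate differences. That is true, and it limits what can be claimed from the fix. It does not make separate significance tests informative about a difference.

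**Conclusion.** The point holds as stated in the heading. For ten factors the SAP plans separate fits and no test of whether the effects differ. If bedtime dosing works equally in everyone at the design HR, each factor has a 50–61% chance of a significant/non-significant pair, and about 91–95% of trials would show at least one. If there is no effect at all, moving to interaction tests gains almost nothing family-wise.

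These figures rest on a true HR of 0.724, 301 events, a two-sided 0.05 level, assumed event splits, and independent factors in the simulation. Real characteristics overlap, so the ten-factor figures are approximate. The separately published protocol that the documents cite was not available to check.

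This should be changed, but it bears on subgroup interpretation only. The primary estimate, the sample size and the stopping rule are untouched.

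**What to change.** Replace the subgroup sentence with the following plan.

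1. For each factor, fit one Cox model in the full cohort with the primary covariate set fixed, plus the factor and the allocation-by-factor term. Sex, CHF, CKD and diabetes are already in the Table 2 list, so only the interaction needs adding for them if the covariate has entered the primary model.
2. Report the ratio of HRs with its confidence interval and the interaction p-value. Take the stratum HRs and intervals from the same model, with no within-stratum p-values.
3. State that the events-per-covariate cap is not reapplied within strata.
4. Label all ten analyses exploratory. Say that about 40% of trials would show at least one nominal interaction by chance, or adjust for multiplicity (for example 0.05/10 = 0.005 per test).
5. State that power is about 20–29% for a ratio of HRs of 0.724, so a non-significant interaction does not show that the effects are equal.

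The cost is a paragraph of SAP text and minor programming, with no new data. The October 2024 chronotype analysis already uses this kind of model.

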### Sensitivity Analyses

- 1) We will conduct a per-protocol analysis by excluding residents from any facility where fewer than 60% of medication doses are taken at bedtime in the intervention group 6-months post implementation.
- 2) We will conduct a full intention-to-treat analysis by including everyone who was initially assigned an allocation, even if they became ineligible (e.g., died) while waiting for their facility to act on the allocation list.

